**A randomised controlled trial TO ASSESS**

**THE LIFESTRAW Family® household gravity filter**

***Study Protocol***

***Department of Infectious and Tropical Diseases***

***London School of Hygiene & Tropical Medicine***

**A. Background**

Diarrhoea is the second most important cause of mortality among children less than 5 in developing counties and claiming 2.5 millions lives each year (Kosek 2003). Interventions to improve water quality at the household level have been shown highly effective in reducing diarrheal diseases (Clasen 2007).

Over the past few years, the WHO has actively encouraged the development of new point-of-use water treatment technologies that are effective, acceptable and affordable to populations in low-income countries. Among the most common methods are chlorination, ceramic filtration, solar disinfection and boiling (Sobsey 2002). However, each of these has limitations. For examples, chlorination is often associated with an unpleasant taste and smell and is less effective in highly turbid water. Ceramic filters can have a slow flow rate and tend to be less effective with small enteric pathogens such as viruses.

To overcome these shortcomings, Vestergaard Fransen SA has developed a new household-based gravity filter system “LifeStraw Family” that uses ultrafiltration mechanisms to remove pathogens. The filtration unit consists of a hollow-fibre cartridge of 20 nm diameter pore size. Untreated water is poured into a 2L container, flows down a 1 m long pipe and becomes purified as it passes through the cartridge. Microbiologically safe water can be directly accessed via a tap. The filter system is designed for suspension on a wall and the length of the pipe was chosen specifically to improve flow rate. The cartridge is also equipped with a backwash inlet to facilitate cleaning of the filtering unit, thus preventing clogging and improving longevity. Independent laboratory testing of the cartridge have shown high microbiological performance, meeting the US EPA standards of 4-log reductions for viruses. The device is designed to last for about a year and to treat up to 10,000 L of water with a flow rate of approximately 6L/hour. The flow shuts down when the hollow-fibres are exhausted, indicating when to replace the cartridge.

**B. Objectives**

The objectives of the study are (i) to assess the effectiveness of the LifeStraw Family household filter in preventing diarrhoeal diseases (ii) to determine the effectiveness of the LifeStraw household filter in reducing the bacterial load of drinking water and (iii) to evaluate the extent to which it is used correctly and consistently by, and is acceptable to, the target population (iv) finally, we will measure longevity of the filter as it is used in a field setting.

**C. Methods**

***1. Trial design and setting***

A two-arm randomised placebo-controlled trial will be conducted over a 12-month period. The trial will include two groups of households: one group receiving the LifeStraw Family filter and the other group receiving a placebo version of the LifeStraw filter. The study will be conducted in a rural setting with poor water supply facilities and the community will be selected based on the following criteria (i) reliance on highly contaminated drinking water sources including unprotected open wells, and surface water sources with contamination levels higher than 1000 TTC/100ml (ii) Low use of household water treatment methods such as boiling, filtration etc. (iii) A high representation of children under 5 in the population (iv) Strong willingness from community members and leaders to take part in the project. The site will be selected following a preliminary site assessment visit during which samples will be taken from water sources and analysed.

***2. Enrolment and randomisation***

Households who are willing to take part of the study are eligible if they don’t treat their water in a way that is deemed effective to prevent diarrhoea (e.g. boiling, filtration with a state of the art filter, regular use of bleach). After being given full details of the study, the head of household will be asked to consent in writing to participate. A copy of the information and consent form is attached as Appendix A. Prior to the commencement of the study; a baseline survey will be conducted. The head of household will be interviewed about family demographics, household possessions (as a measure of estimated wealth), water source, and water handling and purification practices. The baseline questionnaire will be translated into the local language and piloted before use. Following baseline, household participants will be randomly assigned to one of the two groups by using a list of consecutively numbered households and a random number generator or by conducting a lottery. Randomisation will be conducted by a member of staff not involved in the data collection. The study participants and the field investigators will be blinded to group assignment.

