***4. Outcome assessment***

Diarrhoea prevalence

Within one month of distributing the filters, field investigators will visit each household once a month (i.e. 12 visits per household during the overall follow-up period) to conduct a health survey. They will record for each household member, whether she/he had experienced any illness in the past 7 days, prompting a list of symptoms - in which diarrhoea is included - if no answer was spontaneously given. Repeated point prevalence has been shown as more valid and less resource-intensive method for estimating longitudinal prevalence compared with continuous surveillance (Schmidt, 2007). Formative research will be conducted prior to the intervention in order to explore local perception of diseases. Based on these findings, diarrhoea will be self-defined (Ross, 1994) or defined according to the standard WHO definition of 3 or more loose stools in a 24 hr period. Any medical conditions observed by field staff during visits will be referred to the local medical centre.

Microbial water quality, filter use and longevity

In each of the two groups, a random sample of households (25%) will be selected every month to assess microbiological performance of the filters. Field staff will conduct unannounced random visits and will take two samples: one sample of untreated drinking water before it is poured into the filter and one from filtered water coming out of the system’s tap. If the household store the filtered water for drinking, a third sample will be taken from the container in which filtered water is stored. During the visit, field investigators will also fill a brief observations checklist on the filter’s appearance and potential problems encountered with the filter. If the filter is no longer in use, the reason given by the user will be recorded. If the filter has clogged, the time at which the filter went out of service will be noted and the filter will be replaced by a new one. This will be used to assess longevity. All samples for microbiological analysis will be collected in sterile Whirl-Pack™ Bags. Samples will be placed on ice and processed within 4 hours of collection to assess levels of thermotolerant (faecal) coliforms. Microbiological assessment will be performed using the Oxfam-DelAgua Portable Water Testing Kit in accordance with the kit’s instructions.

Acceptability

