**6. Data analysis**

Data will be recorded on an Excel spreadsheet and analysed in Stata software (version 9). The primary analysis will consist of comparing longitudinal prevalence of diarrhoea between the intervention and the control groups.

Secondary analyses include:

- Comparison of faecal coliforms (TTC per 100ml) in the water before and after filtration.
- Assessment of longevity of the filters
- Descriptive analysis of use and acceptability data

Diarrhoea prevalence will be analysed using appropriate statistical procedures which adjust for clustering within household and for repeated measures over time. Multivariate analysis will adjust for potential confounders (e.g. age, level of wealth etc). The quantitative outcomes will be analysed with appropriate parametric and non-parametric methods.

Sample size

The sample size required for meeting the primary objective of the study i.e. detecting a 30% reduction in diarrhoea prevalence among individuals from the intervention group compared to individuals from the control group was calculated based on the following assumptions: a significance level of 0.05 (two-sided), 80% power, a baseline prevalence of diarrhoea of 5%, a coefficient of variation of 2. The following formula was used:

**N** = [(0.84+1.96)2 x (sd02+sd12)] / (p0-p1)2 = **511** Individuals

Where:

- sd0 and sd1 are the standard deviation among the control group and intervention group respectively;
- p0 and p1 are the expected diarrhoea prevalences among control and intervention group.
- Standard deviations were obtained as following: sd0=0.05*2=0.1 and sd1=0.035*2=0.07.

In order to account for lost to follow-up (10%) and clustering of diarrhoea within household, the sample size will be 600 individuals in each arm. Assuming 5 persons per household on average, the number of households to be recruited in each arm is 120 households per arm so approximately 240 households in total.

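### The baseline interview, as listed, omits the 7-day illness recall, so baseline diarrhoea cannot be used to sharpen the primary comparison or to show chance imbalance

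*Protocol*

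**What the plan says.** Protocol, 2. Enrolment and randomisation: a survey precedes the trial, in which the household head is "interviewed about family demographics, household possessions (as a measure of estimated wealth), water source, and water handling and purification practices". The topics are not worded as examples. Allocation comes afterwards: "Following baseline, household participants will be randomly assigned to one of the two groups".

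Protocol, 4. Outcome assessment: health data collection is tied to filter distribution: "Within one month of distributing the filters, field investigators will visit each household once a month (i.e. 12 visits per household". At each visit the investigator records for every member "whether she/he had experienced any illness in the past 7 days", with prompting for symptoms that include diarrhoea. The only disease-related work placed before the intervention is qualitative: "Formative research will be conducted prior to the intervention in order to explore local perception of diseases". It also decides which diarrhoea definition is used.

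Protocol, 6. Data analysis: "Multivariate analysis will adjust for potential confounders (e.g. age, level of wealth etc". Baseline diarrhoea is not named. The sample size uses "a baseline prevalence of diarrhoea of 5" per cent, a coefficient of variation (CV) of 2, a 30% reduction and "a significance level of 0.05 (two-sided), 80% power".

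**The concern.** Every household is already interviewed before allocation, and that is the only time at which diarrhoea can be measured free of the intervention. An analysis plan can add a covariate later only if the data exist, so this gap cannot be closed after the filters go out.

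Two things are lost. The first is precision: a person's own earlier diarrhoea carries some information on later diarrhoea, and the sample size has little slack once household clustering is counted. The second is sight of chance imbalance in the outcome itself, which the listed baseline topics show only indirectly.

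**Working it through.** **Inputs from the protocol (6. Data analysis unless noted).** p0 = 0.05, p1 = 0.035; SDs 0.10 and 0.07 (CV 2); 600 per arm with 10% loss; 5 persons per household; 12 visits (4. Outcome assessment). **Assumptions, not in the protocol:** equal correlation between any two visits of one person; a linear-model variance reduction; household ICC of 0.05 or 0.10.

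**1. The plan's own figure.** (0.84 + 1.96)² × (0.10² + 0.07²) / 0.015² = 7.84 × 0.0149 / 0.000225 = 519, against the stated 511. The difference is 1.6% and does not matter here.

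**2. Correlation between visits implied by the plan, control arm.** One visit has variance 0.05 × 0.95 = 0.0475. The 12-visit mean has variance 0.0475 × (1 + 11r)/12. Setting this to 0.10² = 0.01 gives r = 0.139.

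**3. Value of one baseline recall, control arm.** Its correlation with the 12-visit mean is 0.139 × 0.0475 / √(0.0475 × 0.01) = 0.30, so R² = 0.091.

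**4. Intervention arm.** One visit has variance 0.035 × 0.965 = 0.0338. Setting 0.0338 × (1 + 11r)/12 to 0.07² = 0.0049 gives r = 0.067. Between-person variances are 0.139 × 0.0475 = 0.00659 (control) and 0.067 × 0.0338 = 0.00228 (intervention). The covariance of a baseline recall with the later mean is at most √(0.00659 × 0.00228) = 0.00387, so R² is at most 0.00387² / (0.0475 × 0.0049) = 0.064. Weighted by variance over both arms: (0.091 × 0.01 + 0.064 × 0.0049) / 0.0149 = 0.083. Hence a ceiling of 8 to 9%.

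**5. Overlap with the planned covariates.** Suppose age and wealth explain a share f of the control arm's between-person variance 0.00659. The R² added by baseline diarrhoea is then [(1 − f) × 0.00659]² / [(0.0475 − 0.00659f)(0.01 − 0.00659f)]. The protocol gives no f, so a range is shown:

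| f | added R² |
|---|---|
| 0 | 9.1% |
| 0.25 | 6.4% |
| 0.50 | 3.7% |
| 0.75 | 1.3% |

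Fading correlation over the year acts in the same direction. If the correlation of the baseline recall with the 12-visit mean were 0.1 to 0.2 instead of 0.30, R² would be 1 to 4%.

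**6. Power.** 600 less 10% leaves 540 per arm. The design effect is 1 + 4 × ICC, so the effective n is 540/1.2 = 450 at ICC 0.05 and 540/1.4 = 386 at ICC 0.10. Power = Φ(0.015 / √(0.0149 × (1 − R²)/n) − 1.96). For simplicity the starting power is left at its unadjusted value.

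| R² removed | ICC 0.05 | ICC 0.10 |
|---|---|---|
| 0 | 74.1% | 67.5% |
| 1.3% | 74.7% | 68.1% |
| 3.7% | 75.7% | 69.1% |
| 6.4% | 76.9% | 70.3% |
| 9.1% | 78.1% | 71.6% |

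**7. Chance imbalance.** With 600 per arm at 5%, the standard error of a baseline difference is √(2 × 0.0475/600) = 0.0126 before clustering. At a slope of 0.139, an imbalance of one standard error shifts the outcome contrast by 0.0017, about 12% of the 0.015 target difference.

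**The case against.** The strongest reply is that nothing here is wrong. Randomisation makes the comparison valid without any baseline outcome, and choosing covariates is normally left to the analysis plan. The first part stands and limits the point to efficiency. The second does not answer it, because data never collected cannot be specified later.

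A second reply is that the questionnaire is not shown and the topics come from one summary sentence. That stands as a limit: the point concerns the survey as listed.

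Third, the gain is small. One 7-day report of a 5% event predicts a year's mean weakly, and all ages are enrolled, so age may already carry much of the information. This stands, and it is why 8 to 9% is a ceiling. One reading would raise the ceiling: if CV 2 described true rather than observed individual prevalence, R² in the control arm would be 16%. The plan's formula, however, uses these SDs as those of the quantity compared, which supports the lower figure.

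A reader might also infer that the trial rests on a 5% prevalence it never measures. The protocol does not support this. The 5% is entered as p0, the expected control-group prevalence, and the placebo arm measures that at 12 visits over a year. Nor would a baseline figure test the stated sample size: with CV 2 and a 30% reduction held fixed, p0 cancels, since 7.84 × 4 × (1 + 0.49)/0.09 = 519 at any prevalence. Prevalence matters if the CV moves with it, but one round cannot estimate the CV. What remains is a rough, one-season early check: about 3.8 to 6.2% (95% interval around 5% in 1,200 people without clustering), or 3.3 to 6.7% at an assumed ICC of 0.2.

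**Conclusion.** The point holds as a minor efficiency loss. The listed baseline content leaves out the outcome's own recall, and no other step before randomisation is described that measures it. The variance that one recall could remove is at most about 8 to 9%, and more plausibly about 1 to 6%. At assumed ICCs of 0.05 to 0.10 the ceiling is worth about 4 points of power, and the plausible range about 0.5 to 3.

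These figures rest on equal correlation between visits, on CV 2 describing the observed 12-visit mean, on a linear-model variance formula (the protocol does not fix the model) and on ICCs that the protocol does not give. It would be wrong to conclude that the comparison is biased without the baseline recall, or that adding it would restore 80% power: under these ICCs even the ceiling reaches only about 78% and 72%.

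**What to change.** - In 2. Enrolment and randomisation, add to the baseline interview, before allocation, the 7-day illness recall of 4. Outcome assessment for all household members, with the same wording and prompts.
- In 4. Outcome assessment, state that the formative research is completed and the diarrhoea definition settled before the baseline survey.
- In 6. Data analysis, prespecify individual baseline diarrhoea and age as covariates in the primary model. If the observed baseline prevalence is set beside the 5%, label it as a one-season figure that does not verify the CV.

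The cost is a somewhat longer interview, covering about 1,200 people in 240 households, and a firm deadline for the formative work. No extra visit is needed.

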***3. Study intervention***

Half of the participating households will receive the Lifestraw filter and the other half will receive a filter which looks like the Lifestraw filter but which does not remove pathogens from the water.

The placebo has the same outside components as the real filter but the filtering membranes inside the cartridge have been replaced by some extra piping to imitate the weight of the real cartridge and the flow coming out of it. The 27-micron layer on the pre-filter has been removed to ensure that the placebo does not retain any bacteria. The placebo device has been tested in the laboratory and was shown to be ineffective in removing pathogens from the water.

Households will be trained on how to use their filter according to the manufacturer’s instructions. They will also be advised to continue following their usual drinking water practices so that the use of the placebo is not increasing their risk of drinking contaminated water. No hygiene instructions will be provided to study participants.

***4. Outcome assessment***

Diarrhoea prevalence

Within one month of distributing the filters, field investigators will visit each household once a month (i.e. 12 visits per household during the overall follow-up period) to conduct a health survey. They will record for each household member, whether she/he had experienced any illness in the past 7 days, prompting a list of symptoms - in which diarrhoea is included - if no answer was spontaneously given. Repeated point prevalence has been shown as more valid and less resource-intensive method for estimating longitudinal prevalence compared with continuous surveillance (Schmidt, 2007). Formative research will be conducted prior to the intervention in order to explore local perception of diseases. Based on these findings, diarrhoea will be self-defined (Ross, 1994) or defined according to the standard WHO definition of 3 or more loose stools in a 24 hr period. Any medical conditions observed by field staff during visits will be referred to the local medical centre.

Microbial water quality, filter use and longevity

In each of the two groups, a random sample of households (25%) will be selected every month to assess microbiological performance of the filters. Field staff will conduct unannounced random visits and will take two samples: one sample of untreated drinking water before it is poured into the filter and one from filtered water coming out of the system’s tap. If the household store the filtered water for drinking, a third sample will be taken from the container in which filtered water is stored. During the visit, field investigators will also fill a brief observations checklist on the filter’s appearance and potential problems encountered with the filter. If the filter is no longer in use, the reason given by the user will be recorded. If the filter has clogged, the time at which the filter went out of service will be noted and the filter will be replaced by a new one. This will be used to assess longevity. All samples for microbiological analysis will be collected in sterile Whirl-Pack™ Bags. Samples will be placed on ice and processed within 4 hours of collection to assess levels of thermotolerant (faecal) coliforms. Microbiological assessment will be performed using the Oxfam-DelAgua Portable Water Testing Kit in accordance with the kit’s instructions.

Acceptability

Acceptability of the intervention will be evaluated through questionnaires administered at 4, 8 and 12 months of follow-up. A random sample of the female heads of households will be asked to participate in focus group discussions. All acceptability material such as questionnaires and focus group discussion guide will be piloted before use.

Blinding

Field investigators responsible for conducting health surveys will be different from those involved in filter distribution, filter inspections and water sampling and analyses. During the follow-up, a survey will be conducted among both participants and health surveyors in order to evaluate whether the intervention was successfully blinded.

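### As written, a household member who volunteers another illness is not prompted for diarrhoea, so the primary outcome is ascertained unevenly and probably under-recorded

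*Protocol*

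**What the plan says.** Section C.4 of the Protocol (Diarrhoea prevalence) describes the monthly health survey: "They will record for each household member, whether she/he had experienced any illness in the past 7 days", with the qualification "prompting a list of symptoms - in which diarrhoea is included - if no answer was spontaneously given". The survey is repeated at "12 visits per household during the overall follow-up period".

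This is the only description of how diarrhoea is elicited. The same section leaves the case definition to formative research: "diarrhoea will be self-defined (Ross, 1994) or defined according to the standard WHO definition of 3 or more loose stools in a 24 hr period". That choice settles what counts as diarrhoea, not who is asked about it.

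Section C.6 (Data analysis) rests the main result on these answers: "The primary analysis will consist of comparing longitudinal prevalence of diarrhoea between the intervention and the control groups". The sample size is set for "detecting a 30% reduction in diarrhoea prevalence among individuals from the intervention group", with "a significance level of 0.05 (two-sided), 80% power, a baseline prevalence of diarrhoea of 5%, a coefficient of variation of 2".

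**The concern.** The opening question is about illness in general, and the only diarrhoea-specific probe depends on the reply to it. Read literally, the rule treats members with diarrhoea in three ways:

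- Diarrhoea is volunteered: it is recorded.
- Nothing is volunteered: the list is read, and diarrhoea can be picked up by the prompt.
- Only another illness is volunteered: an answer has been given, the list is not read, and diarrhoea goes down as absent.

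The third group makes sensitivity depend on whether the member has another complaint worth mentioning. Three things could be at stake: the level of recorded prevalence, the power of the comparison and, if the loss differs by arm, the prevalence ratio. No analysis plan can recover the answer to a prompt that was not given, so the matter has to be settled in the questionnaire.

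**Working it through.** **Inputs from the Protocol, section C.6:** p0 = 0.05, p1 = 0.035 (ratio 0.70), coefficient of variation (CV) 2, so sd0 = 0.10 and sd1 = 0.07; two-sided 0.05, 80% power; 511 individuals stated per arm before inflation.

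**Inputs assumed, because the documents give none:** q, the share of members with diarrhoea who volunteer another illness (10% to 30%); m, the share of those whose diarrhoea is then not volunteered (30% to 70%). The prompt is taken to find all other cases. If other illness is unrelated to diarrhoea, q equals its share over all person-visits; if the two tend to occur together, q is larger.

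**1. The plan's own figure.** N = (0.84 + 1.96)² × (0.10² + 0.07²) / 0.015² = 7.84 × 0.0149 / 0.000225 = 519. The stated 511 is within 2% of this, and the difference plays no part here.

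**2. Equal loss in both arms.** Sensitivity = 1 − q × m.

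| q | m | Sensitivity | Recorded control | Recorded intervention | Ratio |
|---|---|---|---|---|---|
| 0.10 | 0.30 | 0.97 | 4.85% | 3.40% | 0.70 |
| 0.20 | 0.50 | 0.90 | 4.50% | 3.15% | 0.70 |
| 0.30 | 0.70 | 0.79 | 3.95% | 2.77% | 0.70 |

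Prevalence and the absolute difference shrink (from 1.5 to 1.35 percentage points in the middle row). The ratio does not move, because both arms are multiplied by the same factor.

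**3. Power under equal loss.** The plan sets each SD at twice the prevalence. If the CV stays at 2, SDs and difference shrink together. In the middle row N = 7.84 × (0.09² + 0.063²) / 0.0135² = 519, as before. Power is lost only if the CV rises. As an illustration, let it rise as 1/√(1 − L), with L = q × m the share of cases missed. Then N = 519 / (1 − L), and power at 511 per arm is Φ(2.778 × √(1 − L) − 1.96), where 2.778 = 0.015 / √(0.0149 / 511).

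| L | N per arm | Power at 511 |
|---|---|---|
| 0 | 519 | 79% |
| 5% | 547 | 77% |
| 10% | 577 | 75% |
| 20% | 649 | 70% |

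That rise is what pure Poisson variation would give. Twelve visits at 5% give 0.6 expected positive visits, hence a Poisson CV² of 1/0.6 = 1.67 against the planned 2² = 4. For cases lost at random the rise should therefore be smaller than shown.

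**4. Unequal loss.** Let q be 25% in one arm and 20% in the other, with m = 0.5 in both. Sensitivities are 1 − 0.125 = 0.875 and 1 − 0.10 = 0.90.

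- More other illness in the intervention arm: (0.035 × 0.875) / (0.05 × 0.90) = 0.68.
- More other illness in the control arm: (0.035 × 0.90) / (0.05 × 0.875) = 0.72.

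If the filter also reduced other complaints, the second line would apply, and a true 30% reduction would read as 28%.

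**5. Scale of that shift.** With CV 2 and 519 per arm, the standard error of the log ratio is √((4 + 4) / 519) = 0.124. The 95% interval around 0.70 is 0.70 × exp(±1.96 × 0.124), about 0.55 to 0.89, before any allowance for household clustering. A shift of 0.02 is small beside it.

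**6. What a large distortion would need.** With 20% of cases missed in control and 10% in intervention, the ratio is (0.035 × 0.90) / (0.05 × 0.80) = 0.79, an apparent 21% reduction. Reversed, it is (0.035 × 0.80) / (0.05 × 0.90) = 0.62, an apparent 38%. Either case needs a twofold difference in missed cases between arms.

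**The case against.** The strongest reply is that the clause compresses a whole interview into a few words. It may have meant that each symptom not mentioned spontaneously is then prompted, and the questionnaire that would settle this is not shown. That is a fair possibility, and it is why the point is about the rule as written. It does not remove the point: a surveyor following the Protocol literally would skip the list, and no other section says that every member is asked about diarrhoea.

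Three stronger readings are tempting, and the documents support none of them.

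- A reader might infer that members with another illness are never asked about the primary outcome. They are asked "whether she/he had experienced any illness in the past 7 days", which covers diarrhoea, and they may mention it alongside a cough or fever. They are not prompted, which is less than not being asked.
- A reader might infer that the cases lost are those of the sickest members. Nothing supports this: volunteering a cough does not mark someone as sicker.
- A reader might infer that the treatment comparison is seriously biased. Equal loss leaves the ratio intact. Against unequal loss, section C.3 provides a look-alike placebo, section C.2 blinds participants and field investigators, and section C.4 (Blinding) keeps health surveyors apart from the staff who handle filters and water samples and plans a check of blinding. Blinding does not exclude a real effect of the filter on other complaints, but it makes a large imbalance in reporting unlikely.

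**Conclusion.** The point holds in a limited form. On the literal wording, diarrhoea is prompted for some members and left to be volunteered by others, according to whether another illness was mentioned first. The expected result is under-recorded prevalence: sensitivity of 79% to 97% over the assumed ranges, and about 90% in the middle. That range rests on assumed values of q and m among members with diarrhoea, and on the prompt finding every remaining case.

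The ratio is preserved if the loss is equal in both arms. Power then falls only if the CV rises above 2, for example to 75% at 511 per arm with 10% of cases missed under the illustrative rise. Bias in the ratio needs a loss that differs by arm, for instance because other illness is volunteered more often in one of them. It is modest under plausible values (0.68 or 0.72 instead of 0.70). The change is worth making because it improves the sole measurement of the primary outcome at almost no cost, not because the planned comparison is invalid without it. It is a cheap improvement, not a must-fix.

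**What to change.** Reword the survey rule in section C.4. Keep the open question first; then read the full symptom list, including diarrhoea, for every household member at every visit, whatever was volunteered. Record each symptom as volunteered or prompted, and count either as diarrhoea in the primary analysis. If the questionnaire already works this way, only the sentence in the Protocol needs correcting.

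The cost is a questionnaire edit and a slightly longer interview at visits already planned. The volunteered-or-prompted flag also shows, by arm, how many cases come to light only through the prompt.

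### Filter longevity is recorded only at visits to a random 25% of households each month, so on the natural reading about a quarter of evenly spread failures are never seen, most of them near month 12

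*Protocol*

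**What the plan says.** Protocol section B makes field longevity of the filter objective (iv), and section C.6 (Data analysis) lists it among the secondary analyses without a method. Data collection is described in section C.4 (Outcome assessment), under microbial water quality, filter use and longevity:

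- Sampling: "a random sample of households (25%) will be selected every month to assess microbiological performance of the filters". This applies in both groups, and the visits are unannounced.
- At a sampled visit staff complete a short checklist. For a clogged filter, "the time at which the filter went out of service will be noted and the filter will be replaced by a new one".
- The protocol then says of this record: "This will be used to assess longevity".

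No other route to longevity data is stated. The monthly visits to all households are health surveys. Under Blinding in C.4, the health surveyors are kept separate from the staff who distribute and inspect filters. Acceptability is assessed by "questionnaires administered at 4, 8 and 12 months of follow-up", which are not linked to filter status.

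The trial lasts 12 months (section C.1), and the Background describes the device as "designed to last for about a year and to treat up to 10,000 L of water".

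**The concern.** A monthly random sample suits microbiological performance, which is a cross-sectional question. Longevity is a time-to-event question, and there each filter's own inspection history matters. A filter that clogs in a household not drawn that month stays unrecorded until the household is drawn, and goes unrecorded for good if it is not drawn again before month 12. The later the failure, the fewer rounds remain to find it. With a nominal life of about a year and 12 months of follow-up, the failures of most interest are the ones most likely to be missed.

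At stake is objective (iv). The longevity estimate would rest on incomplete and partly retrospective failure records, with little information about the last months. An analysis plan can choose how to censor, but it cannot recover failures that nobody observed.

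**Working it through.** The protocol gives no figure for longevity, so there is none to reproduce.

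**Inputs from the protocol.** 25% of households inspected per month (C.4); 120 households per arm (C.6), so about 30 inspections per arm per month; 12 months of follow-up (C.1).

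**Assumptions.** Twelve monthly rounds, one at the end of each month. Each round is an independent draw, so a filter escapes any one round with probability 0.75. The failure-time distributions are assumed, because the protocol gives none.

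**1. Filters never inspected.** 0.75^12 = 0.032, and 0.032 × 120 = 3.8, about 4 per arm. Inspected at most once: 0.75^12 + 12 × 0.25 × 0.75^11 = 0.158.

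**2. Failures never seen.** A failure in month m faces 13 − m remaining rounds, so P(never seen) = 0.75^(13 − m).

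| Month of failure | 3 | 6 | 9 | 10 | 11 | 12 |
|---|---|---|---|---|---|---|
| Never seen by month 12 | 6% | 13% | 32% | 42% | 56% | 75% |

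Average over months 1 to 12: 3 × (1 − 0.75^12)/12 = 0.242. Average over months 7 to 12: 3 × (1 − 0.75^6)/6 = 0.411.

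**3. Delay.** The mean number of rounds until a filter is drawn is 1/0.25 = 4. A failure falls on average half a month before the next round, so the mean delay is 4 − 0.5 = 3.5 months if follow-up had no end. Among failures found within 12 months, simulation gives a mean delay of 1.8 to 2.4 months, depending on the failure distribution.

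**4. Effect on the estimate.** Simulation of 400,000 filters with Weibull life (shape 3, median 12 months); mean life restricted to 12 months:

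| Handling of the data | Restricted mean (months) |
|---|---|
| Truth | 10.27 |
| Accurate out-of-service date, censored at last inspection | 10.27 |
| Accurate out-of-service date, unseen filters counted as working at month 12 | 10.70 |
| Discovery date, censored at last inspection | 10.96 |
| Discovery date, unseen filters counted as working at month 12 | 11.23 |

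When unseen failures count as working, apparent 12-month survival is 70% against a true 50%. Exponential life shows the same pattern. With 30% failing by month 12, the truth is 10.09 and the highest estimate 10.88. With 50% failing, they are 8.66 and 10.00. In both cases an accurate date with censoring at last inspection shows no bias.

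**5. Sampling without replacement in 4-month blocks.** Each filter's last inspection falls in month 9, 10, 11 or 12 with equal probability, leaving 3, 2, 1 or 0 months unobserved. Evenly spread failures missed: [(3 + 2 + 1 + 0)/4]/12 = 0.125.

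**The case against.** **Upward bias is not certain.** A reader might infer that longevity is bound to be overstated. The protocol does not support that: it records when the filter went out of service, not when the failure was discovered, and with accurate dates and censoring at last inspection the estimate is unbiased (step 4). The Background also says flow stops when the fibres are exhausted, which a user can notice. Recall error could go either way, and censoring rules belong in an analysis plan that is not shown. All of this stands. What remains is the loss of observation itself, and the absence of any statement on how the out-of-service time is established.

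**The primary result can still be interpreted.** It is tempting to say that the diarrhoea comparison cannot be read without knowing how many filters worked. That does not follow. A random 25% per group each month estimates the working share without bias, from about 30 × 12 = 360 inspections per arm over the year. The worst-case standard error for one month is √(0.25/30) = 9 percentage points, or about 8 with the finite-population correction.

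**Volume need not be measured.** The 10,000 L figure is a product description in the Background. Objective (iv) does not undertake to test it.

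**A fresh draw is an inference.** The protocol says "In each of the two groups, a random sample of households (25%) will be selected every month", which does not exclude rotation. If the sample rotates through all households every four months, the 24% falls to 12.5% and the first part of the fix only writes down what was intended. The final months would still be thinly observed.

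**Conclusion.** The point holds as a weakness in data collection for a secondary objective. On the fresh-draw reading, about 24% of evenly spread failures (41% if confined to the last six months) are never seen, about 4 of 120 filters per arm are never inspected, and the mean delay is about 3.5 months, ignoring the end of follow-up. Longevity is therefore imprecise, most of all near month 12. It is overstated only if unseen filters are treated as working or discovery dates replace out-of-service dates. These figures assume independent monthly draws, 12 month-end rounds and, for the averages, evenly spread failures. The document does not support a claim of certain upward bias, of an uninterpretable primary result, or of a need to measure volume. A cheap improvement is worth making.

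**What to change.** 1. State in C.4 that the monthly 25% is drawn without replacement within each 4-month block, in random order. Every filter is then inspected three times with the same number of visits, and missed evenly spread failures fall from about 24% to about 12.5%. If the order is re-randomised in each block, the gap between two inspections can still reach 7 months (month 1, then month 8).
2. Have filter-inspection staff record for every household, at the 12-month questionnaire, whether the filter is in service and, if not, when it stopped. State how that date is established.
3. Analyse active-arm filters as interval-censored time from distribution, censored at the last time each was known to be in service.

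**Cost.** A different draw list and two status items. The protocol does not say that the questionnaires reach every household. If they do not, the month-12 check adds up to 120 − 30 = 90 visits per arm.

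**Downsides.** Visits become slightly more predictable within a block. Status questions could threaten blinding if health surveyors asked them, since the placebo has no filtering membranes and clogging could reveal the arm. That is why inspection staff should ask them.
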